### Research design

2.1

This study is a single-assessor-blind, parallel-group, two-arm randomized controlled trial. Participants will be randomly assigned in a 1:1 ratio to either a 12-week aerobic exercise group (AE group) or a non-exercise control group (Con group). Clinical assessments will be performed at baseline (pre-intervention) and at the 12-week follow-up. A detailed schedule of enrollment, interventions, and assessments is presented in **Table 1**. Considering the minimum clinically effective dose of exercise, adherence to the intervention will be defined as the completion of at least 80% of the prescribed exercise sessions. Participants who do not meet this threshold will be categorized as non-adherent. To minimize attrition bias, all participants, regardless of their adherence or completion of the intervention, will be followed up and included in the primary analysis according to the intention-to-treat (ITT) principle. Written informed consent will be obtained from all participants before enrollment. The reporting of this trial will adhere to the Consolidated Standards of Reporting Trials (CONSORT) statement.

**Table 1 T1:** Participant timeline: schedule of enrollment, interventions, and assessments.

Trial period	Enrollment		Post-randomization			Close-out
Timepoint	Screening *(Day-12 to 0)*	Baseline *(Day0)*	Intervention Period *(Weeks 1-6)*	Intervention Period *(Day42)*	Intervention Period *(Weeks 6-12)*	*Week 12 (± 3 days)*
Enrollment:						
Eligibility screen	X					
Informed consent	X					
Medical history	X					
Randomization		X				
Intervention:						
Aerobic Exercise Group		X				X
Control Group		X				X
Assessments:						
Primary outcomes						
nitroglycerin-mediated dilation		X				X
myocardial global work efficiency		X				X
Secondary outcomes						
Energy Metabolism		X				X
Peak Heart Rate (HR_peak_)		X		X		X
Traditional Cardiovascular Risk Factors		X				X
Cardiovascular & Cardiopulmonary Function		X				X
Self-reported fatigue assessment		X				X
24-hour physical activity monitoring		X				X
Circulating biomarkers		X				X
Safety monitoring						
Adverse Events		X				X

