### Intervention

2.7

The exercise intervention for the AE group is structured according to the FITT-VP principle (Frequency, Intensity, Time, Type, Volume, Progression). The protocol aligns with the American College of Sports Medicine (ACSM) guidelines for exercise in patients with T2DM (23). All training sessions will be supervised by certified clinical exercise physiologists. Considering the significant effects of AE on glucose homeostasis, all supervised sessions will be scheduled 1–2 hours postprandially to prevent exercise-induced hypoglycemia.

The exercise intervention consists of a 12-week supervised program with three sessions per week. Each session comprises a 5-minute warm-up (50%–60% of HR_peak_), 50 minutes of aerobic exercise (55%–75% of HR_peak_), and a 5-minute cool-down (50%–60% of HR_peak_). Given the progressive nature of cardiorespiratory adaptations to exercise training, the 12-week program will be divided into an initial phase (Weeks 1–6) and a secondary phase (Weeks 7–12). Cardiopulmonary exercise testing (CPET) will be performed at baseline and at the end of Week 6 to assess cardiorespiratory fitness and to prescribe exercise intensity based on the heart rate peak (HR_peak_). The HR_peak_ is identified as the heart rate corresponding to the achievement of VO_2peak_ during the CPET. For participants receiving heart rate–modulating medications (e.g., β-blockers or non-dihydropyridine calcium channel blockers) or those exhibiting chronotropic incompetence with a blunted heart rate response, exercise intensity will be prescribed using a combination of the power output (Watts) derived from the CPET and the Borg Rating of Perceived Exertion (RPE; target range 12–14). This approach ensures the delivery of a consistent and relatively moderate-intensity training stimulus. Throughout the intervention, participants in the AE group will wear heart rate monitors Polar H7 (Polar Electro, Kempele, Finland) to facilitate real-time monitoring and dynamic adjustment of exercise intensity.

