Participants assigned to the control group (Con group) will not receive any supervised or structured exercise intervention. To ensure a clear distinction from the AE group, they will be explicitly instructed to maintain their habitual lifestyle patterns throughout the 12-week study period. To objectively monitor adherence to these instructions, physical activity levels will be assessed weekly using the International Physical Activity Questionnaire (IPAQ). Any deviations from baseline activity patterns will be documented.

Throughout the 12-week intervention, all participants will be required to maintain their baseline medication regimens. Dosage adjustments will be permitted only when medically necessary for safety reasons (e.g., in cases of severe hypoglycemia or uncontrolled blood pressure), and any such modifications will be meticulously documented.

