### Statistical analysis

2.12

All statistical analyses will be performed using R software (version 4.3.1 or later; R Foundation for Statistical Computing, Vienna, Austria). For the description of baseline data, normally distributed continuous variables will be presented as 
mean±standard deviation (SD), while non-normally distributed variables will be reported as median [interquartile range (IQR)]; categorical variables will be expressed as frequencies and percentages (n, %). For the comparison of baseline data between groups, independent samples t-tests will be used for normally distributed continuous variables, the Mann-Whitney U test will be used for non-normally distributed data, and the chi-square (χ²) test or Fisher’s exact test will be used for categorical data.

Efficacy analyses will be conducted according to the intention-to-treat (ITT) principle and will include all randomized participants. Continuous outcomes, including NMD and GWE, will be analyzed using linear mixed-effects models (LMMs). To rigorously control for potential confounding, background medication use will be prespecified and included as fixed-effect covariates in the models. Medications will be categorized by therapeutic class, with binary indicators (yes/no) created for: (1) glucose-lowering agents (with separate indicators for GLP-1 receptor agonists and SGLT2 inhibitors), (2) antihypertensive medications, and (3) statins. Each LMM will incorporate group, time, and the 
group×time  interaction as fixed effects, with a random intercept for each participant to account for repeated measurements.

Sensitivity analyses will be performed using multiple imputation to assess the robustness of the findings under different assumptions regarding missing data. In addition, a per-protocol (PP) analysis will be conducted as a secondary sensitivity analysis, including only participants with an attendance rate of at least 80%. Secondary outcomes will be considered exploratory and hypothesis-generating; therefore, no adjustment for multiple comparisons will be applied. A two–tailed *P*–value < 0.05 will be considered statistically significant.

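### The per-protocol rule rests on session attendance, which only the exercise arm has, so its one workable reading compares selected exercisers with unselected controls

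*Protocol article*

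**What the plan says.** In section 2.12 (Statistical analysis), "a per-protocol (PP) analysis will be conducted as a secondary sensitivity analysis", and its population is fixed as "including only participants with an attendance rate of at least 80" percent. No arm is named.

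Section 2.1 (Research design) gives the threshold its meaning: "adherence to the intervention will be defined as the completion of at least 80% of the prescribed exercise sessions". Section 2.7 (Intervention) shows who has such sessions. For the exercise arm, "The exercise intervention consists of a 12-week supervised program with three sessions per week". Controls "will not receive any supervised or structured exercise intervention"; instead, "they will be explicitly instructed to maintain their habitual lifestyle patterns throughout the 12-week study period".

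Control behaviour is tracked by a weekly IPAQ, and "Any deviations from baseline activity patterns will be documented". The article does not link that record to the per-protocol set.

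The primary efficacy analysis is ITT in everyone randomised (sections 2.1 and 2.12). The per-protocol analysis stands beside multiple imputation as a sensitivity analysis.

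**The concern.** A per-protocol set should hold each arm to its own protocol. Here the protocol asks exercisers to attend and controls to keep to their usual activity, but the stated rule tests only the first. Exercisers are sorted by something that happens after randomisation, and controls are not sorted at all.

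The article itself gives reasons to expect attendance to be related to outcome. The Discussion names fatigue as a barrier to adherence, and fatigue is a secondary outcome. Section 2.9 postpones sessions for marked discomfort or out-of-range glucose, which may lower attendance in less well participants. Any such exercisers would leave the set with no matching removal among controls.

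At stake is what the analysis can be used for. It is offered as a check on the ITT result. If its own comparison is no longer randomised, agreement between the two says little about robustness.

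**Working it through.** **Step 1. Who can meet the rule.** The only planned figure here is the 80% threshold.
- Exercise arm: 12 weeks × 3 sessions = 36 prescribed. 0.80 × 36 = 28.8, so at least 29 sessions are needed.
- Control arm: 0 sessions prescribed, so the rate is 0/0 and undefined.

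Reading attendance as assessment visits does not help. The primary outcomes are measured only at baseline and week 12, and section 2.1 ties the 80% to exercise sessions.

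**Step 2. The workable reading.** Exercisers with at least 29 of 36 sessions are compared with controls under no criterion. If 20% of the 37 exercisers were excluded (an assumption), the set would be 37 × 0.80 = 29.6, about 30, against up to 37 controls.

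**Step 3. Size of the selection part (assumed inputs).** The document gives no adherence rate; its 10% is dropout. Let *f* be the share of exercisers who are non-adherent and *D* the adherer minus non-adherer difference in mean change that is not due to treatment. Keeping only adherers shifts the exercise mean by *f* × *D*. Assume *D* = 0.5 SD and *f* = 0.10 to 0.30. The SDs (4.0 and 5.6) and planned differences (2.7 and 4.0) come from section 2.5.

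| *f* | Shift (SD) | Global work efficiency, SD 4.0 | Nitroglycerin-mediated dilation, SD 5.6 |
|---|---|---|---|
| 0.10 | 0.10 × 0.5 = 0.05 | 0.05 × 4.0 = 0.20 | 0.05 × 5.6 = 0.28 |
| 0.30 | 0.30 × 0.5 = 0.15 | 0.15 × 4.0 = 0.60 | 0.15 × 5.6 = 0.84 |

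Against the planned differences this is 0.20/2.7 = 7% to 0.60/2.7 = 22% for work efficiency, and 0.28/4.0 = 7% to 0.84/4.0 = 21% for dilation.

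**Step 4. A second model, also assumed.** Let attendance propensity be normal with correlation *r* to outcome change, with the lowest 20% excluded and no true effect. The shift is *r* × φ(z)/0.80 with z the 20th percentile, which is *r* × 0.35. For *r* = 0.1 to 0.5 this gives 0.035 to 0.175 SD, or 0.14 to 0.70 points of work efficiency and 0.20 to 0.98 of dilation. With 30 against 37 participants, a nominal 5% test would reject in about 5.2% to 10.8% of trials.

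**Step 5. Direction.** Steps 3 and 4 assume that adherers would have done better anyway. Retained controls who became active pull the other way. If the same 10% to 30% range applied to them and each gained the full planned 2.7 points (an extreme assumption), the difference would shrink by 0.10 × 2.7 = 0.27 to 0.30 × 2.7 = 0.81 points. That is as large as the selection shift, so the net sign relative to a true per-protocol contrast is open.

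**Step 6. What a comparison with ITT can show.** Active controls are in both analyses, so their effect does not separate the two. What does separate them is removal of low-attendance exercisers, which mixes a real dose effect with selection. The plan gives no means of telling these apart.

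**The case against.** The strongest reply is that this is a condensed article and the analysis is secondary. Read with section 2.1, the 80% rule plainly concerns the exercise arm. How documented control deviations enter the set could be settled in a fuller document that is not shown. Every per-protocol analysis of exercise against no exercise selects on adherence, and nothing in the primary analysis, the sample size or a decision rule depends on this one.

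Much of that stands. The primary result is safe, and the size of any bias is assumed. But the article does not defer the definition: it states one, and that definition can be applied to one arm only, although compliance data for the other arm are collected. A fuller plan could repair this only by adding to the published rule.

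Three stronger readings are tempting and not supported:
- A reader might infer that the per-protocol set contains no controls. The literal wording allows it, but a between-group analysis would not be run that way, and section 2.1 points to the exercise arm.
- A reader might infer that the bias must favour exercise. Step 5 shows why the sign is not established.
- A reader might infer that the analysis carries no information. That goes too far: a marked disagreement with ITT would still call for explanation.

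**Conclusion.** The point holds in limited form. As stated, the per-protocol rule yields exercisers selected after randomisation against unselected controls, so agreement with ITT would be weak support for robustness. That conclusion follows from the text alone.

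The net direction and size of the bias cannot be derived from the document. The 0.2 to 0.6 points for work efficiency (0.28 to 0.84 for dilation) rest on an assumed 0.5 SD adherer difference and 10% to 30% non-adherence, and leave out any opposite pull from active controls. The ITT primary analysis is unaffected. The rule is worth correcting, but it is no threat to the main conclusion.

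**What to change.** 1. State that the 80% attendance criterion applies to the exercise arm (at least 29 of 36 sessions).
2. Give controls a parallel criterion from the weekly IPAQ already collected, for example remaining in the Low category required at entry. This is a second selection after randomisation and rests on self-report, so it makes the arms parallel without restoring randomisation.
3. Adjust for baseline predictors of adherence, such as baseline fatigue. In the planned model, enter them with a time interaction: a main effect alone shifts both visits equally and, in participants with both visits, leaves the group-by-time estimate unchanged.
4. Label the comparison non-randomised.

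Alternatively or in addition, estimate the effect of attendance in all randomised participants with randomisation as the instrument and the fraction of the 36 sessions attended as exposure, controls set to 0. State the exclusion, linear-dose and no-control-contamination assumptions. In its simple form this is the ITT difference divided by mean attendance: at an assumed mean of 0.80, a 2.7-point difference becomes 2.7/0.80 = 3.4, with the interval stretched in about the same ratio and essentially the same test. It should therefore be presented as an adherence-adjusted effect, not as an independent check on the ITT test.

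The cost is a few sentences, slightly more programming and a wider interval. No new data are needed, and recruitment is still under way, so the choice can be fixed before outcomes are analysed.

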## Discussion

3

Energy metabolism is a complex and highly regulated dynamic process. Patients with T2DM are characterized by metabolic inflexibility, which manifests as widespread dysregulation of glucose, lipid, and protein metabolism. AE is a well-established non-pharmacological intervention recognized for its clinical benefits in ameliorating these metabolic abnormalities (24). Given the dynamic nature of energy metabolism, this study will utilize indirect calorimetry to systematically assess systemic energy metabolism in patients with T2DM, including key parameters such as resting energy expenditure, substrate oxidation rates, and metabolic flexibility. Furthermore, considering that humoral regulation plays a central role in maintaining metabolic homeostasis and is frequently disrupted in T2DM, this study will also quantify the circulating levels of cortisol, as well as Sirt1 and FOXO3, which are crucial regulators of cellular energy metabolism.

In addition to metabolic dysregulation, systemic inflammation and oxidative stress are key drivers of the pathological remodeling and cardiovascular dysfunction observed in patients with T2DM. Acknowledging the central role of these processes, this study will comprehensively assess the impact of AE on systemic inflammation and oxidative stress by quantifying a panel of circulating biomarkers, including oxidative stress markers (ROS, SOD, MDA, Nrf2, HO-1, GPX4, NQO1) and inflammatory biomarkers (IL-18, IL-1β, IL-6, TNF-α, CRP, NLRP3). Furthermore, while AE has been shown to ameliorate myocardial remodeling and improve diastolic dysfunction in patients with T2DM, evidence regarding its effects on systolic function remains inconsistent (25, 26). This inconsistency may be partly attributable to the limited sensitivity of conventional systolic indices, such as left ventricular ejection fraction (LVEF), for detecting the subclinical contractile dysfunction that often characterizes early-stage T2DM cardiomyopathy (27). Global longitudinal strain (GLS) has emerged as a more sensitive metric for detecting subclinical myocardial dysfunction, making it a more appropriate endpoint for evaluating systolic responses to AE. This approach is further supported by our previous preclinical work, which demonstrated that AE improves radial strain in diabetic rats (28). Accordingly, this study will utilize GLS to investigate the effects of AE on systolic function in patients with T2DM. Finally, it is critical to recognize that beyond structural and functional impairments, T2DM also induces myocardial metabolic inflexibility. While preclinical studies have shown that AE can ameliorate this metabolic rigidity, clinical evidence in humans remains scarce. Therefore, this study will utilize the novel index of global work efficiency (GWE) to assess whether AE can improve myocardial energetic efficiency in patients with T2DM (29).

Beyond its profound impact on the heart, T2DM also induces pathological vascular remodeling, characterized by arterial wall thickening and increased arterial stiffness, which elevates the risk of atherosclerosis (30). Vascular tone is co-regulated by endothelium-dependent and endothelium-independent (smooth muscle–mediated) mechanisms. Although some evidence suggests that AE can partially ameliorate T2DM-induced endothelial dysfunction, its effects on vascular smooth muscle function remain largely unknown (31). Accordingly, this study will assess NMD to investigate the effects of AE on the endothelium-independent pathway.

The cardiovascular system is governed by complex neurohumoral regulatory mechanisms, and imbalances in these pathways are closely linked to the cardiovascular complications of T2DM. Persistent, low-grade inflammation and oxidative stress can elevate circulating levels of epinephrine and norepinephrine in patients with T2DM. To explore whether AE exerts its cardiovascular protective effects via the modulation of these neurohumoral pathways, this study will measure circulating epinephrine and norepinephrine levels before and after the intervention. Given that catecholamine dysregulation is a key driver of hemodynamic instability, while AE is a well-established intervention for improving blood pressure in T2DM, blood pressure is a dynamic variable with a distinct circadian rhythm. Single, static office blood pressure readings cannot adequately capture overall blood pressure homeostasis. In contrast, 24-hour ambulatory blood pressure monitoring (ABPM) provides a comprehensive, dynamic blood pressure profile, detailing diurnal and nocturnal levels, circadian patterns, and blood pressure variability, allowing for an integrated analysis of neurohumoral and hemodynamic adaptations.

Peak oxygen uptake (VO_2peak_) represents the maximal capacity of this entire integrated process and is one of the most powerful predictors of cardiovascular events and all-cause mortality. Previous studies have consistently shown that even in patients with T2DM who are free of overt cardiovascular disease, VO_2peak_ is reduced by approximately 20–30%, indicating that integrative physiological dysfunction is an early feature of the disease (32). Existing research regarding the effects of AE on VO_2peak_ in T2DM has largely focused on observing improvements in single parameters. While confirming the presence of global functional impairment, this approach has been insufficient to pinpoint the predominant mechanisms responsible for the exercise-induced improvements. Therefore, by concurrently measuring VO_2peak_ and its underlying determinants, this study aims to deconstruct the systemic physiological response into its constituent multi-system components. This will allow us to determine whether improvements in VO_2peak_ following AE are primarily driven by enhanced cardiac function, augmented skeletal muscle oxygen utilization, restored vascular perfusion, or improved autonomic regulation.

Physical inactivity is a common behavioral characteristic of patients with T2DM. This study will therefore utilize accelerometry to objectively monitor 24-hour movement behavior and evaluate the impact of the AE intervention on daily activity patterns of patients with T2DM. Fatigue is a key contributor to this inactivity, but is often overlooked in the design of clinical exercise prescriptions, representing a significant barrier to intervention adherence. The pathogenesis of fatigue in T2DM is multifactorial, involving both central and peripheral mechanisms. Central fatigue is linked to neurotransmitter imbalances, manifesting as reduced central drive. This study will therefore assess the central fatigue state by quantifying circulating levels of key neurotransmitters, including serotonin (5-HT), dopamine (DA), and γ-aminobutyric acid (GABA) (33). Peripheral fatigue, in contrast, is primarily associated with skeletal muscle dysfunction (34). To assess the state of skeletal muscle and peripheral fatigue, this study will measure serum levels of creatine kinase (CK) and myoglobin (Myo). Given the paucity of robust clinical evidence in this area, this dual-pathway assessment aims to systematically elucidate the specific physiological mechanisms by which AE alleviates fatigue in patients with T2DM.

T2DM is a complex metabolic disorder that precipitates metabolic dysregulation and cardiovascular dysfunction at both the cellular and organ levels (35), which in turn progresses to systemic impairments in metabolism and cardiovascular health (4, 36). While AE has been shown to improve the function of individual organs and specific metabolic pathways (37), it remains unclear whether these discrete benefits translate into an improved state of integrated, whole-body physiological function. Therefore, the present study is designed to bridge the gap between organ-level mechanisms and systemic outcomes, integrating the potential mechanisms at the cellular and organ levels to explain AE-mediated functional improvements from a whole-body perspective, aiming to elucidate how AE promotes metabolic and cardiovascular health from an integrative physiological perspective. This approach may provide novel insights for the optimization of clinical exercise management in patients with T2DM.

